## Abstract

**Background:**

Dementia prevalence is predicted to triple to 152 million globally by 2050. Alzheimer’s disease (AD) constitutes 70% of cases. There is an urgent need to identify individuals with preclinical AD, a 10–20-year period of progressive brain pathology without noticeable cognitive symptoms, for targeted risk reduction. Current tests of AD pathology are either too invasive, specialised or expensive for population-level assessments. Cognitive tests are normal in preclinical AD. Emerging evidence demonstrates that movement analysis is sensitive to AD across the disease continuum, including preclinical AD. Our new smartphone test, TapTalk, combines analysis of hand and speech-like movements to detect AD risk. This study aims to [1] determine which combinations of hand-speech movement data most accurately predict preclinical AD [2], determine usability, reliability, and validity of TapTalk in cognitively asymptomatic older adults and [3], prospectively validate TapTalk in older adults who have cognitive symptoms against cognitive tests and clinical diagnoses of Mild Cognitive Impairment and AD dementia.

**Methods:**

**Aim 1** will be addressed in a cross-sectional study of at least 500 cognitively asymptomatic older adults who will complete computerised tests comprising measures of hand motor control (finger tapping) and oro-motor control (syllabic diadochokinesis). So far, 1382 adults, mean (SD) age 66.20 (7.65) years, range 50–92 (72.07% female) have been recruited. Motor measures will be compared to a blood-based AD biomarker, phosphorylated tau 181 to develop an algorithm that classifies preclinical AD risk. **Aim 2** comprises three sub-studies in cognitively asymptomatic adults: (i) a cross-sectional study of 30–40 adults to determine the validity of data collection from different types of smartphones, (ii) a prospective cohort study of 50–100 adults ≥ 50 years old to determine usability and test-retest reliability, and (iii) a prospective cohort study of ~1,000 adults ≥ 50 years old to validate against cognitive measures. **Aim 3** will be addressed in a cross-sectional study of ~200 participants with cognitive symptoms to validate TapTalk against Montreal Cognitive Assessment and interdisciplinary consensus diagnosis.

**Discussion:**

This study will establish the precision of TapTalk to identify preclinical AD and estimate risk of cognitive decline. If accurate, this innovative smartphone app will enable low-cost, accessible screening of individuals for AD risk. This will have wide applications in public health initiatives and clinical trials.

**Trial registration:**

ClinicalTrials.gov identifier: NCT06114914, 29 October 2023. Retrospectively registered.

**Supplementary Information:**

The online version contains supplementary material available at 10.1186/s12883-024-03609-z.

## Background

Dementia has been described by the Lancet 2017 Commission as *“the greatest global challenge for health”* [1]. There are huge personal costs for people living with dementia and their families and huge economic costs for social and healthcare systems. With people living longer than ever before, and age the main non-modifiable risk factor for dementia, the prevalence is predicted to triple to 152 million worldwide by 2050 [1]. This is particularly pertinent in Australia with its rapidly ageing population and the number of Australians diagnosed with dementia doubling in the last decade to over 400 000 [2]. The key strategy to reduce prevalence is prevention [3, 4] as evidence suggests that about 40% of dementia cases are attributable to modifiable risk factors such as physical inactivity, hypertension and smoking [5]. Strategies to modify these risk factors, and clinical trials of new neuroprotective drugs, are likely to have their greatest impact if they target high-risk individuals at the earliest stages of disease [4, 6]. However, there are currently no population-level screening tests to detect the underlying brain pathology of dementia in the earliest stages. This lack of effective screening tools is a major barrier to reducing the prevalence of dementia. The ability to detect early ‘silent’ pathology would revolutionise the effectiveness of prevention strategies from a blunted ‘one size fits all’ approach to early precision targeting of high-risk individuals before cognitive symptoms emerge and before the brain is irreparably damaged.

The most common cause of dementia is Alzheimer’s disease (AD), accounting for 70% of cases [7]. The pathology of AD includes accumulation of abnormal proteins such as amyloid-beta (Aβ) and phosphorylated tau (p-tau) in the brain, together with neuronal degeneration, glial activation, and neuroinflammation [8]. This pathology covertly progresses for about 10–20 years before symptoms (such as poor memory) and signs (such as low scores on cognitive tests) of dementia are evident [5, 8]. Across the disease continuum, there are three key stages of AD pathology: preclinical AD (before any cognitive symptoms or signs emerge), Mild Cognitive Impairment (MCI), which is also called “prodromal AD” (where cognitive decline has occurred but not to the stage to impair functional abilities), and AD dementia. Cognitive tests commonly used clinically, such as the Montreal Cognitive Assessment (MoCA), and the Mini-Mental State Examination (MMSE), lack sensitivity until the MCI stage, when AD pathology has progressed for around 10 years [9, 10]. Specialist biomarkers such as cerebrospinal fluid (CSF) tests and positron emission tomography (PET) brain scans can detect AD pathological changes across the continuum, including in preclinical AD, but are rarely used clinically as they are too expensive, inaccessible, or invasive and would not be suitable for population-level screening [11]. Even with the recent emergence of blood-based biomarkers such as p-tau 181 [12] (that will be used individually, or in combination with others, as the biomarker-defined measure of AD pathology in this study), it remains unclear how accessible, or costly, these will be for widespread use [13, 14]. Thus, there remains an urgent, unmet need for low-cost, population-level tests to detect AD pathology across the continuum, especially in the earliest stages.

For over a decade, it has been recognised that movements of the human body gradually change across the continuum, and this begins in the preclinical AD stage [15]. In particular, there is a substantial body of research assessing how gait (walking) patterns change. Several studies using gait mats and/or wearable movement sensors to precisely analyse gait patterns have shown that it is possible to detect risk of AD pathology in the preclinical stages [16]. For example, in a cohort study of more than 3,500 older adults with normal cognition at baseline, the speed of walking slowed down 7 years before dementia onset [17]. However, gait analysis has several limitations as a population-level test including falls risk, variation with obesity and the need for specialist movement analysis equipment.

An emerging body of new research demonstrates that analysis of hand movements is also sensitive to preclinical AD pathology and may be a more accessible population-level test [18–20]. For example, in a sample of about 70 older adults, Mollica et al. found that speed and variability of repetitive key-tapping hand movements progressively declined in preclinical AD and AD dementia, and that finger tapping variability (a measure of the irregularity of rhythm) positively correlated with a fluid biomarker of AD pathology (CSF Aβ levels) [20]. Our own research, in > 1,200 cognitively asymptomatic older adults, found that key-tapping hand movements were slower, less rhythmic and had longer key-dwell times in those with lower scores on episodic memory tests (a proxy measure of preclinical AD) [19]. Other studies found that hand reaction times correlated with CSF Aβ levels and worsened across the AD continuum [15, 21, 22]. A recent scoping review of 60 studies, comprising 41,800 participants, examined the associations between a wide range of upper limb movements and cognitive impairment and found that, generally, slower and less rhythmic movements associated with cognitive decline, but only 5 studies (with 310 participants in total) examined finger-to-thumb tapping [18].

There is also evidence that analysis of oral movements may be sensitive to AD. Syllabic diadochokinesis (DDK) is a clinical test requiring adults to say ‘pa’, ‘ta’ and ‘ka’ repetitively, in isolation and in combination, so speech pathologists and other clinicians can evaluate the speed, rhythm, accuracy and coordination of lip, tongue, and palate movements respectively [23]. Clinically, the DDK test is used to detect types of motor speech disorders: (i) abnormalities of articulation secondary to weakness or incoordination of the muscles required for speech (dysarthria), and (ii) speech production difficulties due to sequencing or programming of muscles in the absence of weakness or incoordination (apraxia) [24]. Two types of DDK tasks are commonly used: Alternating Motion Rate refers to the rapid repetition of single syllables such as ‘pa’ or ‘ta’ or ‘ka’; Sequential Motion Rate refers to the rapid repetition of syllables in sequence, ‘pa-ta-ka.’ Both tasks are valid and sensitive motor tests and used in the differential diagnosis of adults with a variety of neurological disorders [25, 26]. Alternating Motion Rates are less affected by linguistic factors. However, Sequential Motion Rates are more complex as they require rapid and successive programming of an unfamiliar non-word motor sequence [24].

Recent research suggests that DDK is a biomarker of cognitive decline, with age-related changes in sensory, motor and language systems impairing cognitive processing and task performance [23, 27, 28]. The DDK test is valuable in diagnosing and monitoring functional decline in progressive neurological disorders, such as dementia, but syllabic DDK has never been investigated in preclinical AD and only once before been assessed precisely using computer analysis [29]. Typically, DDK tasks are audio-recorded, then played back for manual and subjective analysis of rate, rhythm, and accuracy by a speech pathologist. In this project, we will develop an online automated version of the clinical test and apply computer technologies to increase efficiency and accuracy of analysis.

The neural basis for motor manifestations in the preclinical stages of AD, and across the disease continuum, remain uncertain. Most motor studies have evaluated gait dysfunction and generally these have found associations between slower walking speeds with higher amyloid burden [30], smaller hippocampal volume (an area of the brain critical for memory function) [31] and prefrontal deactivation [32]. In terms of hand movements, a recent study found people with MCI and AD dementia had slower and less regular key-tapping hand motor performance with the severity of impairment associated with smaller hippocampal volumes but not with global Aβ deposition [33]. A functional MRI study of more than 600 participants also found evidence that the earliest stages of AD are associated with alterations (less network segregation) in the hand and mouth motor areas of the brain as well as the cognitive association areas [34]. Notably, the AD-related network alterations were independent of amyloid pathology, and distinct from aging-related functional network alternations that usually spare sensory-motor systems relative to association systems [35].

Thus, we propose that looking beyond the current definition of dementia – a clinical syndrome of cognitive decline – and instead investigating AD via movement analysis will facilitate the development of a new test that can detect AD across the continuum, including the preclinical phase. Specifically, we plan to combine analysis of repetitive hand movements (finger-to-thumb tapping) with analysis of speech-like movements (through the DDK test) to provide a more sensitive and inclusive means for detecting AD pathology. This ‘multimodal’ approach will use digital video data for finger tapping analysis combined with audio data for DDK data and is expected to improve the accuracy of the test compared to using a single type of test; a scoping review of 46 studies and 11,750 participants found that, applying a multimodal approach improves the sensitivity and specificity of tests to detect AD and other neurodegenerative disorders [36]. In further support of this proposal, it is noteworthy that the hand and lips-tongue-palate areas in the cerebral cortex share a close topographical relationship, suggesting shared movement pathways [37]. We also recognise from our previous research (see TAS Test Project) [38] that co-morbidities mean that some people cannot finger-tap (for example, limited by pain or paralysis) and that analysing a wider range of hand movements, and two types of movement test (speech-like and hand movements) will be more inclusive. However, repetitive hand and speech-like movements have never been specifically investigated together as a test for the preclinical stage of AD, or indeed for any stage of the AD continuum.

We will use cutting-edge Artificial Intelligence (AI) - based technologies, building on our previous research, to automatically analyse hand and speech-like movement from digital video and audio recordings respectively, and to ‘learn’ abnormal patterns of data that are associated with biomarker-defined AD pathology [39–44]. These advanced computer science techniques provide a precise, automated and efficient method of analysis. We previously developed machine learning techniques for measuring finger tapping using laptops and research cohorts i.e. people who do not have cognitive symptoms and found this approach to be feasible and sensitive to cognitive performance [19, 38, 42, 43]. The proposed method of TapTalk is non-invasive and, as the tests are movement-based rather than language-based, we have purposefully considered that they are accessible to culturally and linguistically diverse communities, First Nations peoples, and those with low literacy skills.

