### Extracting hand-speech movement data

We will use deep neural networks and other machine learning methods to develop and train two computer programs that will automatically detect, respectively, hand key points (e.g. finger and thumb tips) in the video data [43], and syllable features in audio recording (Fig. 1). A series of movement features will be extracted in a fixed window period, by (1) experts in hand movement (JA, KL, [name]) and speech-like movements (LG), and (2) deep-learning approach applied directly on processed video data, to analyse their associations with biomarker-defined measures of AD pathology. The processed video data can be the hand-only cropped video or displacement (between fingertip and thumb-tip) over time data extracted from the raw video. Thus, two approaches, expert guided and AI-based ‘deep-learning’, will extract discriminative hand-speech movement features as input data for the multivariable model. The main outcome will be a validated personal computer (laptop and desktop) version of the TapTalk that discriminates preclinical AD from normal ageing in cognitively healthy adults ≥ 50 years old with defined sensitivity and specificity.

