### Statistical analysis

We will use data from 350 of a sample of 500 participants to develop multivariable models that classify data according to risk of preclinical AD pathology. Data from the remaining 150 will determine the externally validated sensitivity/specificity of candidate models in detecting preclinical AD. Hand-speech movement data will be normalised. Participants with blood biomarker levels in the preclinical AD range (e.g., p-tau 181, or a combination of blood biomarkers) will be classified as ‘AD positive’. We will use penalised logistic regression to measure the associations between movement patterns and AD positivity. Covariates may include age, gender, apolipoprotein E ([APOE] a risk gene for AD analysed through blood sampling as part of the ISLAND Project), years of education, and handedness. As a secondary, more agnostic approach, we will use deep learning methods to discover features in movement and speech-like data that map to AD positivity.

We will use cross-validation to avoid overfitting by selecting penalty terms (type and amount of shrinkage applied to coefficients) which optimise the bias-variance trade-off. Bootstrap procedures will be used to estimate model uncertainty. We will externally validate models using data from the remaining 150 participants. Receiver Operating Characteristic (ROC) curves will be plotted against the positive AD cut-off to assess the sensitivity/specificity of movement and speech-like models to discriminate the preclinical AD stage from normal ageing. The model with the highest area under the ROC curve (AUC) will be chosen as the TapTalk algorithm.

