### Sample size justification

The precise combination of blood-based biomarkers used to determine ‘positive’ preclinical AD pathology is yet to be determined as the scientific literature is developing quickly and new biomarkers are being developed regularly. We will review the literature before deciding on the best biomarker test, or combination of tests, that should be used to define AD pathology risk most accurately.

Currently p-tau 181 is considered one of the most accurate blood-based biomarkers for preclinical AD risk and we have therefore based our sample size calculation on this biomarker. As new tests are developed and are likely to be even more sensitive/specific than p-tau 181, the current calculation is a conservative estimate. We estimate that 17% of cognitively normal adults within our cohort have p-tau 181 in the preclinical AD range [55]. There are no tests of DDK compared to AD biomarkers, so we have based all calculations on finger tapping data.

We have performed ROC curve analysis using open data from Mollica et al. to calculate sensitivity and specificity of finger tapping speed and variability to predict CSF p-tau 181 [20]. This showed area under ROC curve (AUC) of 0.75 for a null linear model including age, gender and years of education, but not finger tapping. We calculated that the sample size to compare a screening test with an AUC > 0.90 against the null model requires 60 preclinical AD cases (positive p-tau181) and 290 healthy ageing controls (negative p-tau181). Thus, we will use 350 in the development dataset (expected 60 [17%] preclinical AD cases) and 150 in the validation dataset (expected 25 [17%] preclinical AD cases) to test cut-offs from the development model. The PROBAST tool [56] for assessment of prediction and diagnostic method studies confirms these development and validation strategies have a low risk of bias.

### AIM 2

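### Aim 1 admits cropped hand video as a deep-learning input and selects on AUC alone, so the winning AUC need not reflect movement only

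*Protocol article*

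**What the plan says.** All of this concerns Aim 1 in the Protocol article.

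- **Purpose.** The Background describes AI methods "to automatically analyse hand and speech-like movement from digital video and audio recordings respectively". The hypothesis, under Aims and hypothesis, is that hand-speech movement patterns detect risk of AD pathology.
- **Input.** Extracting hand-speech movement data names two routes to features: expert-guided, and a "deep-learning approach applied directly on processed video data, to analyse their associations with biomarker-defined measures of AD pathology". It continues: "The processed video data can be the hand-only cropped video or displacement (between fingertip and thumb-tip) over time data extracted from the raw video". Which of the two inputs will be used is left open.
- **Label.** Both routes "will extract discriminative hand-speech movement features as input data for the multivariable model". Whatever the network returns is called a movement feature.
- **Status.** In the Aim 1 Statistical analysis, penalised logistic regression comes first. Then: "As a secondary, more agnostic approach, we will use deep learning methods to discover features in movement and speech-like data that map to AD positivity". Age, gender, APOE, education and handedness are covariates that may be included.
- **Selection.** "The model with the highest area under the ROC curve (AUC) will be chosen as the TapTalk algorithm". No other criterion is given.
- **Benchmark.** The Aim 1 Sample size justification says of open data from an earlier finger-tapping study: "This showed area under ROC curve (AUC) of 0.75 for a null linear model including age, gender and years of education". Tapping was not in that model. The figure serves as the comparator for a test with AUC above 0.90 when the sample is sized. It does not reappear in the selection rule.

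**The concern.** A displacement trace holds only movement. A cropped hand video also holds the look of the hand and the quality of the image. It is plausible that these carry information on age, sex and equipment, and the protocol's own figure shows that age, gender and education alone go a long way towards classifying p-tau status. A network told to find whatever maps to AD positivity has no reason to prefer motion over appearance. A rule that looks only at AUC has no means of telling the two apart.

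At stake is what the result means. If part of the winning AUC comes from appearance or equipment, it would still be reported as evidence that movement detects AD pathology. The score might also behave differently on phones, where the images differ from those of home computers.

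**Working it through.** **1. The plan's own figures.** A prevalence of 17% gives 0.17 × 350 = 59.5 cases in development (stated 60) and 0.17 × 150 = 25.5 in validation (stated 25, leaving 125 controls). The 60/290 split cannot be reproduced uniquely, because the article gives no alpha, power or correlation between AUCs. It is consistent with the stated aim: comparing 0.90 with 0.75 with Hanley–McNeil standard errors and independent AUCs, 60/290 gives 89% power at two-sided 5%, and 99% if the AUCs correlate at 0.5. The 0.75 itself cannot be checked, as the dataset is not in the documents.

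**2. How far could appearance alone go?** Assume a binormal model, in which AUC 0.75 corresponds to a separation d′ = √2 × Φ⁻¹(0.75) = 0.954. If a network recovers the demographic score with correlation r and uses no movement, AUC = Φ(r × 0.954 / √2):

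| r (assumed) | AUC |
|---|---|
| 0.6 | 0.657 |
| 0.7 | 0.682 |
| 0.8 | 0.705 |
| 0.9 | 0.728 |

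The range 0.66–0.73 is an illustration only. No document gives a value for r.

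**3. Could such a model win on AUC?** The documents do not say on which data the AUCs are ranked. Take the validation set of 25 cases and 125 controls, and give the appearance-driven model the full 0.75, which is generous to it. The Hanley–McNeil variance is [A(1−A) + (n₁−1)(u−A²) + (n₂−1)(v−A²)] / (n₁n₂), with u = A/(2−A) and v = 2A²/(1+A).

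- At A = 0.75: u = 0.600, v = 0.643, A² = 0.5625. The variance is (0.1875 + 24 × 0.0375 + 124 × 0.0804) / 3125 = 0.00354, so SE = 0.0595.
- At A = 0.70, SE = 0.0622. At A = 0.90, SE = 0.0422.

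The chance that the appearance model shows the higher observed AUC is Φ(difference / SE of difference). Against 0.70 with independent AUCs this is Φ(0.05 / √(0.0595² + 0.0622²)) = Φ(0.58) = 0.72. Letting the correlation between AUCs run from 0 to 0.5:

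| True AUC of movement model | Chance that appearance (0.75) ranks first |
|---|---|
| 0.65 | 87–95% |
| 0.70 | 72–79% |
| 0.75 | 50% |
| 0.80 | 19–27% |
| 0.85 | 4–10% |
| 0.90 | 0.2–2% |

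**4. Would a later step catch it?**

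- The 150 validation participants belong to the same sample of 500 and are recorded in the same way, mostly on their own computers. A shortcut learned in the 350 should carry over.
- Study 2.1 has many phones film one research team member and compares the recordings with motion sensors. That tests a movement trace across devices. It cannot show whether a score depends on whose hand is filmed.
- In Aim 3, age and gender are again only possible covariates.

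**The case against.** The other side has good points.

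- **Cropped video is an option only.** True; the displacement trace is named beside it. But the choice is open, and nothing in the selection rule depends on it.
- **Deep learning is secondary.** True, and the Discussion commits to transparent models that show which motor components discriminate. Whether a secondary model may become TapTalk is not spelled out. However, deep-learning features are said to feed the multivariable model, and the selection sentence excludes nothing.
- **A demographic null model exists.** It does, but only for sizing the sample. If age and gender were always entered, a pure age/sex proxy would add little; the plan makes them optional.
- **Control runs are analysis-plan detail.** Their mere absence from a condensed article would be no finding. The point rests on what the article does fix: the permitted input and the sole selection criterion.

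A reader might also infer more than the text supports:

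- *That the Background sentence is itself at fault.* It is a general statement of intent and is not wrong.
- *That raw audio is open to the same problem through voice pitch.* The extraction section applies direct deep learning to video and assigns audio to syllable-feature detection. No text feeds raw audio to a network.
- *That the choice of smartphone tasks would be misdirected.* Appearance and camera are largely the same across one person's tasks, so they give no systematic preference among them.

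**Conclusion.** The point holds in a limited form. As written, Aim 1 permits a model trained on hand images, labels its output movement, and picks the winner on AUC without requiring a gain over the age/gender/education model that the protocol itself puts at 0.75. The winning AUC could therefore partly reflect appearance or equipment.

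A reader might go further and conclude that a model using no movement at all is likely to be selected. The documents do not support that. It would need the cropped-video option to be taken, the secondary models to be eligible, and the movement models to fall well short of the 0.90 used for sizing: the chance is 0.2–2% against 0.90 and 4–10% against 0.85. It becomes material only if movement models are modest, at 19–27% against 0.80 and 72–79% against 0.70. A partial contribution from appearance is the likelier harm.

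These figures rest on assumptions. That hand images reveal age and sex is an inference. The 0.75 includes education, which an image is not shown to reveal. It also comes from a different study of about 70 people and from CSF rather than blood p-tau 181. The point should be settled before models are fitted; it does not undermine the design.

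**What to change.** In the sections on extracting movement data and on the Aim 1 statistical analysis, state that a cropped-video model, or one using features from cropped video, is eligible to become TapTalk only if it clearly beats both:

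- (a) the same network run on single still frames or time-shuffled frames; and
- (b) the age/gender/education model, refitted in this cohort.

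Otherwise, select from models built on the displacement or key-point data and the syllable features that the protocol already names. Fix in advance what counts as clearly beating, and compare the models on the same participants.

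An outright ban on cropped video is not needed. It would remove the shortcut, but might also discard real movement information that the trace misses.

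**Cost.** Some wording and one extra control run on data already held, with no new recruitment. The reported AUC may be lower. Precision also limits the comparison: with 25 cases and 125 controls, power to separate 0.90 from 0.75 at two-sided 5% is 54% for independent AUCs and 81% at a correlation of 0.5, against 89% and 99% with 60 and 290. Running the eligibility comparison on cross-validated predictions in the development set, and keeping the 150 for the final report, is therefore the better use of the data.
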